### Randomisation

Allocation to the intervention or control group will be carried out by randomisation of health facilities (clusters). This will ensure the inclusion of an urban and peri-urban site in both the intervention and control groups (i.e. stratification). In both countries, clusters will be geographically separated to reduce the potential for contamination.

### Intervention arm: the thriving Mamas programme

The Thriving Mamas programme aims to support adolescent girls’ wellbeing during pregnancy and the year after birth. The programme consists of nine meetings delivered in either group (5 meetings), individual (1 meeting), or family group (2 meetings) formats over 10 weeks with an additional individual meeting 10–12 weeks postpartum (see Fig. 3). The intervention will be provided in addition to usual perinatal care. Each meeting focuses on physical and mental health, taking care of a newborn, life skills, planning for the future, and harnessing social support. Girls identified as requiring additional support will be referred to health and community-based services. The programme is facilitated by 1–2 women recruited from the local community who have been previously pregnant. Meetings will take place in a mixture of private settings in health facilities, community facilities, and participant homes. Each meeting will last between one and two hours. All mentor mothers will receive training over three to five days to deliver the programme.

**Fig. 3 Fig3:**
[figure not shown]
Thriving Mamas programme overview

### Control arm

Adolescents randomised to participate in the control arm of the trial will receive usual care provided in each country. Each visit includes care that is appropriate to the overall condition and stage of pregnancy and should include four main categories of care:Identification of pre-existing health conditions.Early detection of complications arising during pregnancy.Health promotion and disease prevention.Birth preparedness and complication planning.

In both arms, all participants will be screened for depression and anxiety during pregnancy and after participation in intervention sessions. Adolescents who screen positive for depression or anxiety will be referred for further assessment and care, where needed. Disclosure of or suspected gender-based violence will be provided with information on their rights and where to seek support based on local care provision in each country.

### Variables and data collection procedures

An overview of the assessment tools and measures used to collect the variables of interest to this study and data collection timepoints is provided in Table 1. In line with current best practice in implementation research [16], the research team will evaluate implementation variables as assessed by adolescent girls, mentor mothers, and friends/family members. This offers a 360-degree implementation evaluation, which considers needs and perspectives that typically differ between groups. Quantitative data will be collected through self-report (mentor mothers) or an interview with a member of the research team (adolescent girls, friends/family members, mentor mothers). Qualitative interviews will be conducted by one member of the research team, audio recorded, and last up to one hour.

**Table 1 Tab1:** Variables of interest, assessment periods, and data collection timepoints

Variable	Measure [no. items]	Timepoint												
		Training		Intervention meetings										
		Pre	Post	Pre	1	2	3	4	5	6	7	8	9	Post
**Mentor Mother—trained to deliver the intervention**														
**Sociodemographic**														
*Age*	Sociodemographic questionnaire [7]	X												
*Area of residence (neighbourhood)*		X												
*Marital status*		X												
*Number of children*		X												
*Adolescent pregnancy*		X												
*Education status*		X												
*Occupation*		X												
**Training**														
*Knowledge*	Intervention topic quiz [16]	X	X											
*Attitudes*	Attitudes towards adolescent pregnancy [4] Social Distance Scale (SDS) [12]	X	X											
*Competency*^a^	Question on delivery of the intervention [1]		X											
*Acceptability*^a^	Acceptability of Intervention Measure (AIM) [4]		X											
*Feasibility*^a^	Feasibility of Intervention Measure (FIM) [4]		X											
*Appropriateness*^a^	Intervention Appropriateness Measure (IAM) [4]		X											
*Qualitative Interview*	Semi-structured interview		X											
**Intervention content and delivery**														
*Recruitment rate*	Programme notes			X										
*Retention rate*	Programme notes				X	X	X	X	X	X	X	X	X	
*Referral Rate*	Programme notes			X				X					X	
*Acceptability*^a^	Acceptability of Intervention Measure (AIM) [4]		X											X
*Feasibility*^a^	Feasibility of Intervention Measure (FIM) [4]		X											X
*Appropriateness*^a^	Intervention Appropriateness Measure (IAM) [4]		X											X
*Fidelity*^a^	Adolescent retention rate (fidelity of receipt)				X	X	X	X	X	X	X	X	X	
	Enhancing Assessment of Common Therapeutic Factors (ENACT) [10] (delivery fidelity; collected from adolescent girls)												X	
*Cost of intervention*	Time taken to be trained and deliver the intervention; cost of materials for delivery		X											X
*Qualitative Interview*	Semi-structured interview		X											X
**Adolescent girls**														
**Sociodemographics**														
*Age*	Sociodemographic questionnaire [12]			X										
*Neighbourhood*				X										
*Household members*				X										
*Marital status*				X										
*Parity*				X										
*Education*				X										X
*Employment*				X										X
**Health and wellbeing**														
*Depression*^a^	Patient Health Questionnaire (PHQ-9) [9]			X				X					X	
*Anxiety*^a^	Generalised Anxiety Disorder (GAD-7) [7]			X				X					X	
*Quality of life*^a^	WHO Quality of Life short version (WHOQoL-BREF) [26]			X										X
**Social support**														
*Social support*^a^	Multidimensional Scale of Perceived Social Support (MSPSS) [12]			X										X
**Parenting competency**														
*Parenting competency*^a^	Parenting Sense of Competence Scale [17]													X
**Health behaviours**														
*Perinatal appointment attendance*^a^	Information on attendance to appointments will be based on self-report by adolescent girls			X				X						X
*Referral uptake*^a^	Information on attendance to appointments will be based on self-report by adolescent girls													X
*Infant vaccination*	Health behaviours questionnaire [1]			X										X
*Breastfeeding*	Health behaviours questionnaire [1]			X										X
*Intended time to next pregnancy*^a^	Health behaviours questionnaire [2]													X
*Contraceptive use*^a^	Health behaviours questionnaire [2]													X
**Intervention content and delivery**														
*Acceptability*^a, b^	Acceptability of Intervention Measure (AIM) [4]							X						X
*Appropriateness*^a, b^	Intervention Appropriateness Measure (IAM) [4]							X						X
*Perception of intervention*^a, b^	Tailored questionnaire [6]			X	X	X	X	X	X	X	X	X	X	
*Provider Competency*^a, b^	Enhancing Assessment of Common Therapeutic Factors (ENACT) [10]												X	
*Qualitative interview*	Semi-structured interview													X
**Friends/family members**														
**Sociodemographics**														
*Age*	Sociodemographic questionnaire [7]						X				X			
*Gender*							X				X			
*Relationship to adolescent*							X				X			
*Living with adolescent*							X				X			
*Marital status*							X				X			
*Education status*							X				X			
*Employment status*							X				X			
**Intervention content and delivery**														
*Acceptability*^a^	Acceptability of Intervention Measure (AIM) [4]													X
*Appropriateness*^a^	Intervention Appropriateness Measure (IAM) [4]													X
*Perception of intervention*^a^	Tailored questionnaire [5]						X				X			
*Qualitative interview*^b^	Semi-structured interview													X

^a^*Qualitative interview topic*

^b^Completed only by adolescent girls receiving the intervention

#### Implementation variables

##### Recruitment, retention, and referral rates

Recruitment data will be collected by staff at health facilities and mentor mothers. Recruitment site staff will collect data on the number of adolescents who meet the inclusion criteria and the number who agree to be contacted by a mentor mother. Mentor mothers will collect data on the number of adolescents whom they meet with the numbers who provide consent. Reasons for not consenting will be recorded. Retention and referral rates will be extracted from mentor mother meeting records.

##### Acceptability, appropriateness, and feasibility

Acceptability, appropriateness, and feasibility of the Thriving Mothers programme and training will be assessed among mentor mothers, adolescent girls in the intervention arm, and friends/family members using the Acceptability of Intervention Measure (AIM), Intervention Appropriateness Measure (IAM) and Feasibility of Intervention Measure (FIM), respectively [17]. These brief, four-item tools were developed by implementation experts and display good psychometric properties in high-resource settings. They have been selected as they are commonly assessed in feasibility and pilot studies and, therefore, can be used to compare the intervention’s potential for scale-up with other interventions. Assessment of training will be completed by mentor mothers pre- and post-training. Assessment of the intervention will be completed pre- and post-intervention among mentor mothers and post-intervention among adolescents and friends/family members. Additional data will be obtained post-intervention through semi-structured qualitative interviews with mentor mothers, adolescents, and friends/family members.

##### Fidelity

Data on the number of sessions attended by girls and their friends/family members will be collected from mentor mothers. Attendance records completed by mentor mothers will be used to assess fidelity of intervention receipt. The extent to which the intervention was delivered as intended by the mentor mothers will be assessed by adolescent girls using the Enhancing Assessment of Common Therapeutic Factors (ENACT) tool post-intervention [18]. Qualitative interviews with mentor mothers and adolescent girls will provide a deeper understanding of these issues.

##### Operating costs

The time taken to be trained and provide the intervention as well as the costs associated with delivery (e.g. materials, transport, refreshments) will be estimated by the research team to derive operating costs for economic evaluations.

#### Mentor mothers

Information on the impact of training and delivering the intervention will be collected from mentor mothers pre- and post-training.*Knowledge*: Mentor mothers’ knowledge of issues regarding pregnancy, childbirth, caregiving, mental health, and referral pathways will be assessed using a study-specific quiz based upon the intervention manual.*Attitudes towards mental health*: The Social Distance Scale (SDS) was designed by Bogardus [19] to measure the level of acceptability of various types of social relationships between Americans and members of common ethnic groups [20, 21]. A modified SDS has been widely used to measure mental health-related stigma and to understand the importance of labels attached to people with former mental illnesses [20, 22]. The modified version consists of questions that represent social contact with different degrees of distance. The SDS measures the acceptability of different degrees of social distance and thus, by inference, the attitude of the respondent to the person with the condition [23, 24]. The SDS total score represents the attitude of the respondent towards the condition.The SDS will be used to determine the level of stigma associated with mental health among mentor mothers. As the intervention will address risk factors of poor mental health and support positive mental health among adolescents, it is important that they do not hold negative attitudes towards mental health and those living with mental health conditions. Among stigma measures, it has been shown to most strongly associate with health worker competence [25].*Attitudes towards adolescent pregnancy and mental health*: Four questions were developed for the study to assess mentor mothers’ attitudes towards adolescent pregnancy.

#### Adolescent girls

A variety of variables will be collected from adolescents by mentor mothers and/or a member of the research team at pre-intervention, meeting 4 and post-intervention to investigate the impact of the intervention.*Depression*: Depression is the primary outcome for our study. The Patient Health Questionnaire (PHQ-9; [26, 27]) is a self-administered screening instrument for common mental disorders. The PHQ-9 is the depression module, which scores each of the 9 DSM-IV criteria as “0” (not at all) to “3” (nearly every day). The PHQ-9 has been validated in Kenya [28] and Mozambique [29].*Anxiety*: The Generalised Anxiety Disorder (GAD-7) measure is a seven-item screening tool for anxiety disorder. Each item scores a symptom of anxiety from “0” (not at all) to “3” (near every day). A GAD-7 score ≥ 10 indicates moderate to severe anxiety. The GAD-7 has been validated in Kenya [30] and Mozambique [31].*Quality of life*: Quality of life will be assessed using the short version of the WHO Quality of Life brief version (WHOQOL-BREF; [32]). The WHOQOL-BREF assesses a respondent’s perceived quality of life across four domains: physical health; psychological; social relationships; and environment. Its 26 items are scored on a five-point Likert scale with higher scores indicating greater agreement. The items are allocated to each domain to provide domain scores with higher scores indicating greater quality of life in a particular domain. The WHOQOL-BREF has been used with adolescents in Kenya [33].*Social support*: The Multidimensional Scale of Perceived Social Support (MSPSS) is a 12-item scale which measures social support from family, friends, and significant others [34]. Each item scores the extent to which the respondent agrees with the statements on a Likert scale with “1” (very strongly disagree) to “7” (very strongly agree). The scale has been validated in adolescents in Ghana [35].*Parenting competency*: The Parenting Sense of Competency Scale is a 17-item scale to measure parents’ perceived parenting abilities [36]. The items are rated on a 6-point Likert response scale from “strongly disagree” to “strongly agree.” Overall parenting competence is derived from a total score where higher scores indicate greater perceived competence. The scale has been used to evaluate parenting competence among mothers of infants aged 2–12 months [37, 38].*Service utilisation*: Antenatal appointment attendance information will be collected from adolescent girls through two questions (i.e. How many antenatal appointments were you scheduled to attend since our last meeting? How many of those appointments did you attend?). Uptake of referrals to community services will be collected from adolescent girls through three questions (i.e. Have you been referred to any community services by your intervention provider? If yes, which services have you been referred to? If yes, have you made contact with these services?).*Health behaviours*: Family planning intentions will be assessed using quantitative questions regarding actual or intended contraception use and intended time to next pregnancy. Actual or intended breastfeeding and infant vaccinations will also be collected through a single question for each variable to determine the impact of the intervention on these behaviours.*Provider competency*- The Mentor mothers’ competency will be assessed using the ENACT tool which was adapted to improve relevance to the study. ENACT tool measures a set of therapeutic competencies required for the effective intervention, including the delivery by the non-specialists [39].

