#### Mentor mothers

Up to 16 women will be recruited in each country (total of 32 women across the project) to be trained to deliver the intervention (see Fig. 2). The following inclusion criteria will be used: (a) aged 20 years or older; (b) female; (c) experience of pregnancy and/or parenting; and (d) live within the study site. Women will be excluded from participating if they are unable to attend training or deliver the intervention sessions. Following training, eight women in Mozambique and four women in Kenya will be selected to provide the intervention within the pilot study. Selection will be based on knowledge and attitude scores obtained after training.

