#### Adolescent girls

Up to 40 adolescent girls will be recruited in each country (*n* = 80), through participating community services and health facilities. In Kenya, adolescents will be recruited from local dispensaries. In Mozambique, adolescents will be recruited from primary health centres. The following inclusion criteria will be used: (a) up to 28 weeks pregnant; and (b) aged 15–19 years. They will be excluded from the study if they are unable to provide informed consent or are unable to participate in the intervention, due to existing health conditions.

Adolescent girls who meet the study inclusion criteria will be given information about the study by health facility staff. Those interested in participating will be introduced to a member of the research team, who will provide them with an information sheet and consent form. Where an adolescent is aged 15–17 years, the research team also will discuss the information with their guardian during the same visit, if the guardian is in attendance. If the guardian is not present, a member of the research team will discuss the information sheet with the minor. If she indicates further interest in participating, we will explain that we also require guardian consent due to her age. Following introduction to their guardian, the study will be introduced using the information sheet and consent requested. In this situation, the minor will be required to provide their assent following guardian consent.

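### The protocol allows programme deliverers to collect girls' outcomes, and it ties retention, referral and PHQ-9/GAD-7 timing to meetings and a provider that control girls do not have

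*Protocol article*

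**What the plan says.** **Who collects the girls' outcomes.** The Adolescent girls section under Variables and data collection procedures says that the variables used to study impact "will be collected from adolescents by mentor mothers and/or a member of the research team". The list that follows includes PHQ-9, which that section calls the primary outcome, GAD-7 and the ENACT rating of mentor mother competency. The opening of Variables and data collection procedures instead gives girls' quantitative data to "an interview with a member of the research team (adolescent girls, friends/family members, mentor mothers"; there, mentor mothers appear only as respondents.

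**Who mentor mothers are.** The Mentor mothers section under Participants and sampling method recruits women "to be trained to deliver the intervention". Of up to 32 trained, twelve (eight in Mozambique, four in Kenya) are to deliver it. On the other arm, the protocol says: "Adolescents randomised to participate in the control arm of the trial will receive usual care provided in each country". No mentor mother or programme meeting is described there, although girls in both arms are screened for depression and anxiety and referred if positive.

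**Timing.** Table 1 marks PHQ-9 and GAD-7 at Pre, Meeting 4 and Meeting 9, and leaves Post blank. The Adolescent girls section gives the last assessment as post-intervention. The Control arm section times the later screening, in both arms, by participation in intervention sessions.

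**Retention, referral and consent.** "Retention and referral rates will be extracted from mentor mother meeting records". The referral-uptake question reads: "Have you been referred to any community services by your intervention provider". On consent, the recruitment section says: "Mentor mothers will collect data on the number of adolescents whom they meet with the numbers who provide consent". The sampling section says that interested girls "will be introduced to a member of the research team, who will provide them with an information sheet and consent form".

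**The concern.** PHQ-9, GAD-7 and ENACT are all answered by the girl herself. If the woman who ran her sessions asks the questions in one arm and a researcher asks them in the other, the arms may be assessed differently. The Quantitative analysis section reports PHQ-9 and GAD-7 as adjusted mean differences between arms with 95% confidence intervals, so any such difference enters the estimate. ENACT matters even without an arm comparison. It is the measure of delivery fidelity, fidelity is among the pilot's primary outcomes under Data analyses, and as written a girl may rate her mentor mother's competence to that same mentor mother.

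The second problem is that several items rest on a source, time point or wording that fits only the intervention arm: retention and referral rates from meeting records, PHQ-9 and GAD-7 at numbered meetings, and a referral question about an intervention provider. Retention is a progression criterion and the basis of the sample-size statement, and neither is restricted to one arm. Control retention or referrals left unrecorded during the study cannot be recovered in the analysis.

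**Working it through.** **1. Reproduce the stated precision.** Participants and sampling method gives 80 girls, 32 mentor mothers, 33% loss to follow-up, and 95% limits of ±11% and ±17%. The Wald half-width is 1.96 × √(p(1 − p)/n).

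| Method | n = 32 | n = 80 |
|---|---|---|
| Wald, p = 0.33 | 16.3 | 10.3 |
| Wald, p = 0.5 | 17.3 | 11.0 |
| Exact (10–11 of 32; 26–27 of 80) | 16.9–17.3 | 10.7–10.8 |

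The exact method, or Wald at p = 0.5, rounds to the stated 17 and 11. So ±11% requires follow-up status on all 80 girls. Clustering is ignored throughout.

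**2. Precision if meeting records were the only source.** The Friends/family members section allows one guest per intervention girl and gives n = 40, so about 40 girls have meeting records. Like for like:

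- Wald, p = 0.33: 1.96 × √(0.33 × 0.67/40) = 14.6 points, against 10.3.
- Wald, p = 0.5: 15.5 points, against 11.0.
- Exact, 13 of 40: 15.3 points, against about 10.8.

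**3. The progression criterion from that source.** Suppose retention is 67% in the 40 intervention girls (26.8 girls) and unknown in the 40 controls. Overall retention then lies between 26.8/80 = 33.5% and (26.8 + 40)/80 = 83.5%. The 67% threshold cannot be judged for all 80 girls from meeting records.

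**4. What Table 1 does with retention.** Retention is marked at Meetings 1 to 9, not at Post, and adolescent retention rate appears again as the measure of fidelity of receipt. That is session attendance. The progression criterion is defined at endline assessment. One word covers two quantities, and the only named source serves the first.

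**5. Timing.** The programme has 5 group, 1 individual and 2 family meetings over 10 weeks (5 + 1 + 2 = 8), plus an individual meeting 10–12 weeks postpartum. Meeting 9 therefore appears to be the postpartum one, although the overview figure is not shown. Control girls have no Meeting 4 or Meeting 9, and the article fixes no equivalent dates for them.

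**6. Referral item.** Table 1 uses footnote b for items completed only by intervention girls. Referral uptake does not carry it, so the item is meant for both arms. A control girl referred after a positive screen can truthfully answer no, because she has no intervention provider. The question on contact is asked only after a yes, so she drops out of the denominator and her referral is not captured.

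**7. Consent.** In the sampling section a research team member gives the information and seeks consent. In the recruitment section, site staff count girls who agree to be contacted by a mentor mother, and mentor mothers count those who consent. These are two different procedures.

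**8. Possible size of assessor bias (assumed values only).** If a share s of intervention-arm endline PHQ-9 scores is taken by mentor mothers and this shifts answers by b points, the arm difference moves by s × b. With s from 0.25 to 1 and b from 0.5 to 2, that is 0.125 to 2.0 points. The documents give neither s nor b.

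**The case against.** The strongest defence is that the article already contains the right procedures. The and/or wording permits collection by mentor mothers but does not require it, and the opening of the same section assigns the girls' interviews to the research team. PHQ-9, GAD-7, quality of life and social support carry no footnote b, and screening is stated for both arms. A reader might infer that control outcomes are missing by design; the documents do not support that. Nor do they support saying that missing outcomes follow session attendance: Meetings 4 and 9 are column labels for time points, nothing makes assessment conditional on attending, and quality of life is in the Post column.

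Other tempting readings also go too far. A bias in favour of the intervention is plausible but not shown. Control referral uptake is uncaptured or undefined, not 0%. Setting 14.6 against the stated 11 mixes two methods. That mentor mothers work only in the intervention arm is a strong inference from their role, not a statement, and the consent passage is not limited to one arm, so control consent data are not shown to be lost.

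The defence also notes that endline retention could be taken from the assessments themselves, that the pilot is not meant to detect a treatment effect, and that no progression criterion uses a PHQ-9 difference. All of this is fair. It does not remove the conflict over who collects, the deliverer's possible role in her own ENACT rating, the lack of a named control-arm source for retention and referral, the referral wording, or the conflict on consent. ENACT and retention feed a primary outcome and a progression criterion, so the pilot's limited aim does not excuse them.

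**Conclusion.** The point holds as a set of conflicts and one-arm sources that must be reconciled before recruitment. The protocol permits programme deliverers to collect girls' self-reported outcomes, including ratings of themselves, and contradicts this elsewhere. The resulting risk of differential assessment is real, but its size and direction are unknown. PHQ-9 and GAD-7 timing is unclear for control girls. Retention and referral rates are drawn from records that would cover about 40 girls. If nothing else were used, precision on loss to follow-up would worsen from 10.3 to 14.6 points (Wald, p = 0.33) or from about 10.8 to 15.3 (exact), and the 67% criterion could not be judged for the whole sample. Control referrals go uncaptured by the item as worded, and the two accounts of consent disagree.

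This rests on three assumptions: about 40 girls per arm, no mentor mother meeting records for control girls, and no allowance for clustering.

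**What to change.** 1. State that research team members who do not deliver the programme collect all girl-reported outcomes in both arms, and also ENACT, which only intervention girls complete. Remove mentor mothers as collectors from the Adolescent girls section.
2. Set PHQ-9 and GAD-7 assessments by calendar windows common to both arms, and align Table 1, the Adolescent girls section and the Control arm section.
3. Compute retention from the endline assessment log in both arms. Report session attendance separately, as fidelity of receipt. Name a source for referral rates that exists in both arms.
4. Reword the referral item to cover referral by any health worker, study staff or programme facilitator.
5. Reconcile the recruitment section with the sampling section on who obtains and counts consent.

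The changes are to wording and mostly adopt what the article already says about research team interviews, research team consent and endline retention. The cost is a little more interviewer time for the existing research team wherever mentor mothers would have collected data.

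### The service-use questions never measure postnatal attendance, have no fixed recall window, and tie referral uptake to a provider that control girls do not have

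*Protocol article*

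**What the plan says.** Table 1 of the protocol article, under Health behaviours, lists "Perinatal appointment attendance" at Pre, meeting 4 and Post, and referral uptake at Post. Both rows give the same source: "Information on attendance to appointments will be based on self-report by adolescent girls". Neither row carries the footnote that restricts an item to girls receiving the intervention.

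The Adolescent girls section, under service utilisation, narrows the first variable: "Antenatal appointment attendance information will be collected from adolescent girls through two questions". The first question is "How many antenatal appointments were you scheduled to attend since our last meeting", and the second asks how many of those were attended. Referral uptake has three questions. The first is "Have you been referred to any community services by your intervention provider"; the other two are asked only if the answer is yes. All of these are presented as the items themselves, not as examples.

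The intervention section describes eight meetings over 10 weeks, "with an additional individual meeting 10–12 weeks postpartum". That is meeting 9, and Table 1 has a separate Post column after it. The Control arm section says that in both arms "Adolescents who screen positive for depression or anxiety will be referred for further assessment and care, where needed".

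**The concern.** Three features of the wording do not fit the schedule or the two-arm design.

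- The variable named in Table 1 is perinatal, the endline is postpartum, and the questions are antenatal.
- The recall window is anchored to a meeting that is not identified. Intervention girls have nine programme meetings and control girls have none.
- The referral item presupposes an intervention provider.

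Health behaviours fall under Objective 2, which explores the impact of the intervention, and the Adolescent girls section says that these variables are collected for that purpose. The pilot is also meant to inform the design of the full trial. Items that miss part of the construct, or that mean something different in each arm, would distort the descriptive results and could be carried forward unchanged.

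**Working it through.** The article states no figure on this point to reproduce. The check sets the item wording against the schedule and the arm descriptions, with simple timeline arithmetic.

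**1. Construct against timing.** Table 1 says perinatal; the text says antenatal. Post follows a meeting at 10–12 weeks postpartum. No quoted item asks about appointments after birth, so postnatal attendance is unmeasured at every timepoint.

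**2. How much of the endline window is lost, if the anchor is the meeting 4 assessment.** Inputs from the article: entry at up to 28 weeks of pregnancy, main programme of 10 weeks, meeting 9 at 10–12 weeks postpartum. Assumptions: birth at 40 weeks, meeting 4 in programme week 3 to 5, programme start at entry, and Post at the time of meeting 9 (a later Post would raise the share). With *g* = weeks of gestation at entry, *w* = programme week of meeting 4 and *p* = weeks postpartum at Post:

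postpartum share = *p* / (40 − *g* − *w* + *p*)

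| Entry *g* | Lowest share (*w* = 3, *p* = 10) | Highest share (*w* = 5, *p* = 12) |
|---|---|---|
| 12 | 10/35 = 29% | 12/35 = 34% |
| 20 | 10/27 = 37% | 12/27 = 44% |
| 24 | 10/23 = 43% | 12/23 = 52% |
| 28 | 10/19 = 53% | 12/19 = 63% |

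On this reading, antenatal visits from meeting 4 to birth are still counted: 7 to 9 weeks for a girl entering at 28 weeks (40 − 28 − 5 and 40 − 28 − 3). The item is incomplete at Post, not empty.

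**3. If the anchor is the last programme meeting.** At Post this is meeting 9. The whole window is then postpartum, and an intervention girl has 0 antenatal appointments scheduled and 0 attended; the attended proportion is 0/0. A control girl, with no programme meetings, can only answer back to an earlier research contact. The windows then differ by arm. The article does not settle which reading applies. It allows either mentor mothers or the research team to collect the data, so the person asking may be the one who ran the meetings. At Pre, neither reading gives a referent.

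**4. Referral uptake.** Control girls receive usual care alone and have no intervention provider, so their only truthful answer to the first question is no. The conditional questions are then skipped and uptake is never asked. Control uptake is zero over all girls (0/40 if the 80 are split equally) and undefined among referred girls (0/0), whatever referrals they received. Yet the Control arm section provides for referral in both arms. The article's other referral data come from mentor mothers' meeting records, which belong to programme delivery, so no source described in it captures control-arm referrals. In the intervention arm, referrals made by anyone else are missed too.

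**The case against.** **Attendance can still be compared.** The same questions go to both arms at the same three timepoints, and in a repeated assessment the natural reading is since the previous assessment. On that reading antenatal attendance up to birth is comparable. This stands: a reader might infer that attendance cannot be compared at all, or that the endline count must be zero, but both follow only from the programme-meeting reading. The omission of postnatal visits is untouched.

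**The referral item may be a programme process measure.** Referral is part of the programme, and the intervention-only footnote is used unreliably: it is also attached to the friends and family interview, where it makes no sense. This weakens the inference that control girls were meant to answer. Even so, the row as printed applies to all girls, and it needs either a label or a broader question.

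**No between-arm analysis is planned.** The regressions name only PHQ-9 and GAD-7, the pilot is declared to be descriptive, both variables are also interview topics, and neither is a progression criterion. This stands and limits the harm.

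**No count of missed referrals can be given.** A reader might apply the article's estimate of 1 in 3 adolescents with a perinatal mental disorder to 40 control girls and conclude that about 13 referrals would be lost. That figure is a prevalence over pregnancy and the following year, not a screen-positive or referral rate. The item also concerns community services, whereas screening leads to further assessment and care where needed.

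**Conclusion.** The point holds in limited form. Postnatal attendance is unmeasured although Table 1 names a perinatal variable at a postpartum endline; this needs no assumption. The recall anchor is undefined at Pre and ambiguous afterwards. The loss at Post is about 29–63% of the window if the anchor is the meeting 4 assessment, under the timing assumptions above, and the whole window for intervention girls if it is meeting 9. Control-arm referral uptake is a structural zero or undefined, so it has no valid comparison with the intervention arm.

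A reader might infer a general bias in favour of the intervention. The article supports that direction only for referral uptake, and only if the arms are compared. For attendance no direction is established: on the programme-meeting reading, the zero counts fall in the intervention arm. Nor is it right that control girls cannot answer the referral question; they can, but the answer carries no information. What is affected is the descriptive evidence under Objective 2 and the instruments passed to the full trial.

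**What to change.** - **Attendance:** ask separately about antenatal and postnatal appointments, scheduled and attended. Count antenatal visits since the dated previous research assessment, and postnatal visits since that date or since birth. Use the same wording and anchor in both arms, and give the Pre question its own defined start. Use one term for the variable in Table 1 and the text.
- **Referral:** ask whether the girl has been referred to any service by anyone, record the source (for example facility staff, research team or mentor mother), then ask about contact made. Alternatively, mark referral uptake in Table 1 as intervention-only and do not compare it across arms.

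The cost is rewording the existing items and adding one or two short ones, with no extra visits. The article reports no recruitment as of September 2023, so on its own timetable the change could precede data collection. If the forms have already been used, report attendance as antenatal only, state the anchor that interviewers applied, and present referral uptake for the intervention arm alone.
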